## Abstract

**Background:**

Adults with attention deficit hyperactivity disorder (ADHD) often present with a lifelong pattern of core symptoms that is associated with impairments of functioning in daily life. This has a substantial personal and economic impact. In clinical practice there is a high need for additional or alternative interventions for existing treatments, usually consisting of pharmacotherapy and/or psycho-education. Although previous studies show preliminary evidence for the effectiveness of mindfulness-based interventions in reducing ADHD symptoms and improving executive functioning, these studies have methodological limitations. This study will take account of these limitations and will examine the effectiveness of Mindfulness Based Cognitive Therapy (MBCT) in further detail.

**Methods/design:**

A multi-centre, parallel-group, randomised controlled trial will be conducted in *N* = 120 adults with ADHD. Patients will be randomised to MBCT in addition to treatment as usual (TAU) or TAU alone. Assessments will take place at baseline and at three, six and nine months after baseline. Primary outcome measure will be severity of ADHD symptoms rated by a blinded clinician. Secondary outcome measures will be self-reported ADHD symptoms, executive functioning, mindfulness skills, self-compassion, positive mental health and general functioning. In addition, a cost-effectiveness analysis will be conducted.

**Discussion:**

This trial will offer valuable information about the clinical and cost-effectiveness of MBCT in addition to TAU compared to TAU alone in adults swith ADHD.

**Trial registration:**

ClinicalTrials.gov NCT02463396. Registered 8 June 2015.

## Background

Attention Deficit Hyperactivity Disorder (ADHD) is a common neurodevelopmental disorder with a high persistence into adulthood. Results of a meta-analysis of six studies indicated the pooled prevalence of adult ADHD according to DSM-IV criteria to be 2.5 % (95 % CI 2.1-3.1) [1]. In a Dutch population the prevalence of adult ADHD has been found to be 2.1 % (95 % CI 1.4-3.0) [2]. Patients with ADHD show a persistent pattern of inattention and/or hyperactivity-impulsivity, which leads to impairment of functioning in two or more areas in daily life, for example at work, school and/or home. These impairments have a substantial personal and economic impact. A recent study shows that ADHD is associated with increased mortality, mainly driven by deaths from unnatural causes like accidents [3]. Furthermore, adult ADHD is related to higher levels of unemployment and those who are employed often experience workplace impairment and reduced productivity [4]. In an international population ADHD is associated with 22 days of excess lost role performance among employees a year [5] and with elevated risk of high number of days out of role (OR = 2.6, 95 % CI 2.0-3.5) [6]. Results of a recent survey in a Dutch general population sample showed that adults with ADHD had significantly more functional impairments and an increased health care use than persons without ADHD [2].

The vast majority of ADHD patients in the Netherlands is offered stimulant medication after or parallel to psycho-education on ADHD. In accordance with the NICE guideline on ADHD [7] stimulants are the first-line treatment for adults as part of a comprehensive treatment programme that addresses psychological, behavioural and educational or occupational needs. The pooled effect size of stimulant medication in reducing ADHD symptoms was in the medium-to-high range [8]. Stimulants demonstrated efficacy and they seemed to improve work productivity [9]. Moreover drug treatment in ADHD seemed to have a protective effect on the risk of criminality [10] and suicidal behaviour [11]. Although pharmacological treatment has thus shown to be effective in reducing ADHD symptoms and to have beneficial effects, about 10-30 % of adults with ADHD do not adequately respond to stimulants [12] and often report adverse effects like decreased appetite, dry mouth, tension or jitteriness [13], which can lead to discontinuation. It has also been found that these patients were compliant with medication for rather a brief period (M = 49.5 days), and the average persistence with medication was less than a year (M = 199.9 days) [14]. Besides, some patients with ADHD are not willing to take medication at all. Furthermore, the evidence for long-term effects of stimulants is sparse [15]. Therefore, there is a strong need for evidence-based psychosocial interventions, as an addition to or an alternative for pharmacological treatment of adult ADHD.

The NICE guideline recommends group Cognitive Behavioural Therapy (CBT) for adults with ADHD whose response to medication is insufficient, who have difficulty adhering to drug treatment or who are not willing to use medication. Some studies have shown evidence for the efficacy of treatment with CBT in adults with ADHD, particularly when combined with medication [16]. For example, Safren et al. [17] found support for the effectiveness of individual CBT for patients with ADHD, who are treated with medication but continue to have residual symptoms, compared to a time-matched comparison treatment. Another study of Solanto et al. [18] showed that meta-cognitive group therapy, which is a cognitive-behavioural intervention, provides significant benefit to patients with ADHD with respect to the severity of ADHD symptoms in comparison with supportive group therapy. However, more controlled research studies are required. Another promising psychosocial intervention for patients with ADHD is Mindfulness-Based Cognitive Therapy (MBCT), which combines methods of CBT and mindfulness meditation. Mindfulness is defined as paying attention in a particular way: on purpose, in the present moment, and non-judgmentally [19]. MBCT is usually offered in a group format, consisting of 8 weekly sessions of 2,5 hours and a silent day [20], which may be more cost-effective than individual treatment. In recent years, mindfulness based therapy, such as MBCT, has been demonstrated to reduce anxiety, depression and stress in a wide range of psychiatric disorders [21], including current anxiety and depressive disorders [22]. Furthermore, there is evidence that mindfulness meditation strengthens attention regulation [23–25] and improves some executive functions [26] in healthy subjects. Although these studies were not focused on patients with ADHD and replication studies need to be carried out, this is promising evidence in the search for an effective non-pharmacological treatment for this patient group.

A few studies on the effectiveness of mindfulness training for adults with ADHD have so far been conducted, two uncontrolled pilot studies [27, 28] and two randomised controlled trials (Hepark, Janssen, De Vries, Schoenberg, Kan, & Speckens: The effects of Mindfulness-Based Cognitive Therapy on core sympotms and executive functioning in adults with ADHD: a preliminary randomised controlled trial, submitted) [29]. The studies of Zylowska et al. [27] and Mitchell et al. [29] used the 8-week Mindful Awareness Practices (MAPs) for ADHD programme [30], while our own group [28] (Hepark et al., submitted) used an adapted and extended MBCT programme. All of these studies observed a substantial reduction of primary ADHD symptoms, and the effect of mindfulness training on ADHD symptoms seems to be mediated by an increase of mindfulness skills (Hepark et al., submitted). Moreover, improvements of executive functioning (Hepark et al., submitted) [29] and emotion regulation [29] were reported. In both pilot studies [27, 28] improved executive control was observed using neuropsychological tasks, but this was not replicated in the two randomised controlled trials. Empirical evidence regarding the reduction of secondary symptoms, like depressive and anxiety symptoms and general functioning, is mixed [27, 28] and (Hepark et al., submitted). Possibly, this is partially due to baseline differences in levels of secondary symptoms in the various samples.

The results of the above mentioned studies support the feasibility and efficacy of mindfulness training as a treatment for adults with ADHD and encourage further research. This approach offers a novel and potentially useful tool in the multimodal treatment of ADHD. Previous studies are conducted in one centre and lack a follow-up period. Some of them are small [27–29], uncontrolled [27, 28] and lack blinding [27–29]. The proposed study is the first properly powered randomised controlled multi-centre study, which includes blinded outcome assessments, a longer term follow-up period and assessment of cost-effectiveness.

### Aims of the trial

The primary aim of this study is to investigate effectiveness of MBCT in addition to Treatment As Usual (TAU) versus TAU alone in adults with ADHD. We expect that MBCT can improve ADHD symptoms and overall functioning in two ways: a) by strengthening their attention regulation and executive functioning, resulting in a greater reduction of ADHD symptoms rated by a blinded clinician (primary outcome) and self-reported ADHD symptoms and a greater improvement of executive functioning (secondary outcomes); and b) by extending their repertoire of coping strategies to deal with core symptoms and functional impairments, resulting in a greater improvement of general functioning, positive mental health and self-compassion (secondary outcomes).

Other aims of the study are to assess whether MBCT is a cost-effective intervention compared to TAU in patients with ADHD from a societal perspective and to assess the financial consequences of implementing mindfulness training in patients with ADHD from different perspectives (e.g. societal, health care, health insurance and patient). We expect that the implementation of this intervention will result in a reduction of medical and societal costs in the MBCT group compared to the TAU group.

Furthermore, in order to gain insight in the working mechanisms of mindfulness, we will investigate whether possible clinical effects of MBCT can be attributed to changes in mindfulness skills, self-compassion and adherence to MBCT.

## Methods/design

### Study design

The design of the study is multi-centre, parallel-group, randomised controlled superiority trial. Patients will be randomised to MBCT in addition to TAU or TAU alone. The study protocol has been ethically approved by CMO Arnhem-Nijmegen for all participating centres and registered under number 2014/206.

### Participants

The study population will consist of adults with ADHD. To enhance generalisability, the study is conducted in three different mental health centres for patients with ADHD in the south-east of the Netherlands: the Department of Psychiatry of the Radboudumc in Nijmegen, the Reinier van Arkel Group in the Jeroen Bosch hospital in ‘s Hertogenbosch and Dimence in Deventer. Each centre has a specialized outpatient clinic for adults with developmental disorders, like ADHD.

#### Eligibility criteria

We will include patients of 18 years and older who meet the following criteria: a) a primary diagnosis of ADHD, according to the criteria of Diagnostic and Statistical Manual of Mental Disorders – 4^th^ edition (DSM-IV-TR) [31] based on a structured Diagnostic Interview for ADHD, in adults (DIVA) [32]; and b) capable of filling out questionnaires in Dutch. Exclusion criteria will be: a) depressive disorder with psychotic symptoms or suicidality; b) current manic episode; c) borderline or antisocial personality disorder; d) substance dependence; e) autism spectrum disorder; f) tic disorder with vocal tics; g) learning difficulties or other cognitive impairments; and h) former participation in a MBCT or MBSR course or workshop of more than two hours’ duration. We will use a psychiatric structured diagnostic interview (MINI-Plus) [33] to establish whether patients meet the above mentioned exclusion criteria a, b and d. To assess the third exclusion criterion, screening lists for borderline and antisocial personality disorders based on the Structured Clinical Interview for DSM-IV Axis II Disorders (SCID-II) [34] will be administered. In patients meeting five or more criteria on one or both of the lists, the entire interview for borderline and/or antisocial personality disorder of the SCID-II will be conducted.

### Procedure and treatment allocation

Recruitment will take place in different ways: by referral via the specialist outpatient clinics of the three participating centres and by self-selection. Currently and formerly treated patients with ADHD at the Radboudumc, the Reinier van Arkel Groep and Dimence will be informed about the study by their attending clinicians in various stages of their treatment process. Patients will also be recruited by self-selection by media advertisements, for example through the website of the Dutch association of adults with ADHD (Impuls & Woortblind) and in presentations at regional thematic meetings. Interested patients will receive an information leaflet and are invited for a screening by telephone with the researcher or research assistant to assess eligibility. If patients seem to be eligible, they will get one to two weeks time to consider participation. Patients who chose to participate will be invited for an interview with the researcher or research assistant in which written informed consent will be obtained.

When the Diagnostic Interview for ADHD in adults (DIVA) has not been conducted to diagnose ADHD before, it will be administered by a psychologist or psychiatrist with relevant experience with this specific patient group to check whether a patient indeed meets the DSM-IV criteria for ADHD. Whenever possible the interview will take place in the presence of a family-member, partner or significant other to enable retrospective and collateral information to be ascertained simultaneously.

Blinded assessments with the investigator-rated screening version of the Conners’ Adult ADHD Rating Scale (CAARS-INV) will be obtained by trained psychiatrists or specialist registered nurses (in training) at baseline, 3, 6 and 9 months after baseline. The 6 and 9 months follow-up assessments will take place by phone. Self-report questionnaires will be administered at all of the above mentioned four time points. In order not to disadvantage patients randomised to the TAU group, we will offer them MBCT after completion of the study at 9 months follow-up.

Patients will be able to use medication for ADHD such as psycho-stimulants, during the entire study and they will not be withheld from other psychosocial treatments they might be offered. Concurrent interventions will be closely monitored and registered. See Fig. 1 for a flowchart of the recruitment and study procedure.

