### Sample size

The power calculation has been based on our previous randomised controlled study consisting of 103 adults with ADHD (Hepark et al., submitted) in which we demonstrated a significant difference in post-assessment clinician-rated ADHD symptoms (CAARS-INV) [36] between the MBCT and waitlist control group. Based on these study results, we expect a post-treatment difference of 4 between the two groups with a standard deviation of 7.5. Using a two-sided test with an alpha of 0.05, a power of 80 % and analyzing the data using ANCOVA assuming the correlation between pre- and post-assessments to be 0.5, we would need approximately 45 patients per arm. Taking account for loss of power due to drop out of 25 %, we intend to include 120 patients, 60 patients per group.

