### Statistical analyses

#### Primary analyses

Baseline socio-demographic and clinical characteristics of the MBCT group and the TAU group will be compared to check whether these characteristics will have been evenly distributed by randomisation. The primary analyses will be aimed at comparing results on the outcome measures at three months after baseline between the MBCT group and the TAU group, controlling for baseline levels and possible other baseline differences between intervention and control groups (despite randomisation).

The outcome data will be analysed and reported according to the CONSORT guidelines and will include both intention-to-treat analyses and per-protocol analyses with the treatment-adherent sample (patients in the MBCT group have to attend at least four of MBCT sessions and patients in the TAU group do not attend a mindfulness-based programme). Percentages of improved, recovered, unchanged and worsened patients in the intervention and control groups will be provided on the basis of predefined cut-off scores (*T-*score greater than 65) and standard deviations. In addition, a Cohen’s *d*-type effect size will be calculated.

In order to investigate consolidation of treatment effect at 6 and 9 months after baseline, we will study whether there is an intervention by time interaction with a mixed model to accommodate for repeated measures. Such an interaction would imply that long term effects are different from short term effects. In addition, regression models will be used to derive prediction models for therapy outcome.

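### For the clinician-rated CAARS, short- versus long-term follow-up coincides with a switch to telephone rating, so an intervention-by-time interaction does not by itself show that long-term effects differ

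*Protocol article*

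**What the plan says.** Procedure and treatment allocation schedules the blinded CAARS-INV "at baseline, 3, 6 and 9 months after baseline" and adds: "The 6 and 9 months follow-up assessments will take place by phone". The mode at baseline and 3 months is not stated. That those ratings are in person is an inference from the contrast, and the flowchart (Fig. 1) could not be consulted. The same section says "Self-report questionnaires will be administered at all of the above mentioned four time points" and states no change of mode for these questionnaires.

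Under Primary analyses, the main comparison is "comparing results on the outcome measures at three months after baseline between the MBCT group and the TAU group". The two later visits are handled separately, to see whether the effect consolidates, and the method is this: "we will study whether there is an intervention by time interaction with a mixed model to accommodate for repeated measures". The interpretation is then fixed: "Such an interaction would imply that long term effects are different from short term effects". The section does not mention the telephone ratings, and it does not say what a non-significant interaction would mean.

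**The concern.** The interaction is meant to compare the treatment effect soon after the course (3 months) with the effect later (6 and 9 months). For the CAARS-INV that is also where the rating mode appears to change. No later rating is in person and no earlier one is said to be by phone, so these data cannot separate time from mode. The stated rule attributes any interaction to time alone.

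What is at stake is the durability claim. The Discussion presents six months of follow-up after treatment as an advance on earlier studies. A mode effect of the wrong kind could make a lasting effect look as if it had faded, or a fading effect look maintained.

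**Working it through.** **1. The layout for the CAARS-INV**

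| Visit | Rating mode | Use in the analysis |
|---|---|---|
| Baseline | in person (inferred) | covariate |
| 3 months | in person (inferred) | primary, short-term effect |
| 6 months | phone | long-term effect |
| 9 months | phone | long-term effect |

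Time and mode split at the same place. Both arms switch together.

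**2. What the interaction estimates**

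Let D3 and DL be the true MBCT minus TAU differences at 3 months and at a later visit (negative means benefit). Suppose a phone score equals k × (in-person score) + c, plus d in the MBCT arm only. Then:

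- observed later difference = k × DL + d
- interaction = k × DL + d − D3

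The common shift c drops out. The interaction equals DL − D3 only when k = 1 and d = 0.

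**3. The plan's own figures**

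Sample size gives "we expect a post-treatment difference of 4 between the two groups with a standard deviation of 7.5", two-sided alpha 0.05, power 80%, pre-post correlation 0.5, about 45 per arm, and 60 per group after 25% drop-out.

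- Adjusted SD = 7.5 × √(1 − 0.5²) = 6.50
- n per arm = 2 × [6.50 × (1.96 + 0.84) / 4]² = 41.4, so 42; the t-based version gives 43
- 45 / 0.75 = 60 per group

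The stated size is reproduced closely enough. It concerns the post-treatment comparison and is not in question.

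**4. Assumed mode effects**

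Simulation of 3 months against one later phone visit: 45 per arm, SD 7.5, correlation between the two visits 0.5 (assumed), D3 = −4, 8,000 replicates. The values of k, c and d are assumptions.

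| Scenario | Expected interaction | Rejection rate |
|---|---|---|
| Common shift, c = −3 | 0 | 5.0% |
| Rescaling, k = 0.8, no true change | −3.2 + 4 = 0.8 | 8.7% |
| Rescaling, k = 0.6, no true change | −2.4 + 4 = 1.6 | 21.3% |
| Arm-specific, d = 1, no true change | −3 + 4 = 1.0 | 9.8% |
| Arm-specific, d = 2, no true change | −2 + 4 = 2.0 | 24.3% |
| True loss of 2, no mode effect | −2 + 4 = 2.0 | 23.9% |
| True loss of 2, d = −2 | −2 − 2 + 4 = 0 | 4.9% |

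A true loss of 2 points and an arm-specific shift of 2 points give the same interaction and practically the same rejection rate. The contrast cannot tell them apart.

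**5. The test with no mode effect at all**

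SE = 7.5 × √(2(1 − ρ)) × √(2/45), where ρ is the assumed correlation between post-baseline visits.

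- ρ = 0.5: SE 1.58, 95% half-width 3.1, power for a loss of 2 points 24%
- ρ = 0.8: SE 1.00, 95% half-width 2.0, power 52%

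Using the mean of 6 and 9 months instead, with SD factor √(1.5(1 − ρ)), power is 31% to 64%.

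**6. The randomised difference within one visit**

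If the baseline correlation of 0.5 also holds at 6 or 9 months, SE = 6.50 × √(2/45) = 1.37 and the 95% half-width is 1.96 × 1.37 = 2.7. An observed 4-point benefit would have an interval of about 1.3 to 6.7. This estimate compares patients rated in the same mode.

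**The case against.** The strongest reply is that the bias is hypothetical. Both arms change mode at the same visits, so a simple phone shift cancels, and the simulation confirms it. Harm needs a rescaling or an arm-specific effect, and the document gives no evidence of either. This stands. It limits the point to what the interaction can prove and rules out any statement that the long-term results will be biased.

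A reader might take the investigator-self intraclass correlations (.45 to .87, under Primary outcome measure) as evidence that phone ratings drift towards unblinded self-report. They are not: they compare who rates, not how the interview is held. The CAARS-INV is described as an interview, so in-person scores also draw on what the patient says.

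A reader might also infer that the plan treats a non-significant interaction as proof of consolidation. It does not say so. The caution is worth writing down because the test's stated purpose invites that reading, but the main reason is low power, with rating mode second.

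Finally, the analysis section covers the outcome measures generally. The self-report scales have no stated mode change, so the objection does not reach the sentence as applied to them.

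**Conclusion.** The point holds for one outcome and one inference. On the CAARS-INV, an intervention-by-time interaction across 3 versus 6 and 9 months does not by itself imply that long-term and short-term effects differ, because rating mode changes at the same point. In the assumed scenarios, mode effects that rescale or differ by arm produce spurious interactions of 0.8 to 2.0 points, with rejection rates of 9% to 24%, or fully mask a true loss of 2 points.

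This rests on in-person rating at baseline and 3 months, which is inferred, and on mode-effect sizes and a between-visit correlation that are assumed.

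It would be tempting to conclude that the follow-up results are invalid or that the visits must be redesigned. The documents do not support that. The 3-month primary analysis and the sample size are unaffected. The comparisons at 6 and 9 months remain randomised and same-mode. An arm-specific rating bias, if there were one, could enter them, but they do not depend on phone and in-person scores being interchangeable. This is a modest correction of interpretation, worth making because durability is one of the trial's stated contributions.

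**What to change.** Under Primary analyses, for the CAARS-INV, replace the sentence on what an interaction would imply with a plan along these lines:

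1. Judge durability from the baseline-adjusted MBCT minus TAU differences at 6 and at 9 months, each with a 95% confidence interval, from the mixed model already planned, and label them as phone-rated.
2. If a 3-month versus 6- and 9-month interaction is reported, state that rating mode changes between these visits and interpret it in that light. Do not read a non-significant interaction as consolidation.
3. Present the same 3-, 6- and 9-month analysis of the self-report CAARS-S:SV as the mode-stable check. It is unblinded, so it supports the clinician rating and does not replace it.
4. State the mode of the baseline and 3-month ratings.

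This costs a few sentences and no new data. The price is a somewhat weaker claim about change from 3 months to later follow-up.

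A single mode throughout is not required. All-phone would alter the primary 3-month rating, and all-in-person would add visits in a trial already allowing for 25% drop-out. The 6- versus 9-month contrast shares one mode but does not answer whether the 3-month effect persists.
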